**Methods:**

The study is designed as a randomized, double-blind, 2-arm parallel-group, sham-controlled, trial. Forty-eight participants with SCZ and cognitive impairment (measured via a set of executive functions tests) will be randomly allocated to receive either a single session of active (n = 24) or sham (n = 24) tDCS (20-min, 3-mA). The anodal and cathodal electrodes are positioned over the left and right DLPFC respectively. The stimulation occurs concurrently with the working memory task, which is initiated precisely 5 minutes after the onset of tDCS. Structural and resting-state (rs-fMRI) scans are conducted immediately before and after both active and sham tDCS using a 3 Tesla scanner (Siemens Prisma model) equipped with a 64-channel head coil. The primary outcome will be changes in brain activation (measures vis BOLD response) and working memory performance (accuracy, reaction time).

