While non-invasive brain stimulation techniques are safe methods for directly modifying brain functions in humans and studying the causality of brain-behavior relationships [17], neuroimaging methods, including functional magnetic resonance imaging (fMRI), enable the study of brain function in vivo. Combining these methods allows for experimental induction of alterations in neural processes that have impacts on cognition and underlying physiological processes, as well as assessing cognitive brain correlations [17, 18]. the cognitive benefits of tDCS in SCZ partly rely on the dosage of stimulation [4, 19], which is also observed in healthy populations [20]. Recent physiological findings suggest that an intensified protocol with anodal tDCS (3 mA) can induce longer-lasting and stronger aftereffects on motor cortex plasticity [21], which is also transferred to the prefrontal cortex [22]. Furthermore, for the cognitive effects of stimulation, it is important to consider its effects on functional networks [23]. While previous studies have shown that tDCS can improve cognition in a dose-dependent manner in SCZ [19], the physiological mechanisms underlying these effects have not been fully elucidated. Given the importance of stimulation intensity for cognitive outcomes, it is relevant to evaluate the efficacy of an intensified 3mA tDCS protocol, which has not yet been studied in SCZ, to the best of our knowledge.

This study was designed to investigate the effects of online 3-mA prefrontal tDCS on working memory and the associated brain physiology in patients with SCZ. Specifically, the objectives of the present study were to examine (1) changes in working memory task performance during online 3-mA tDCS in SCZ, (2) changes in blood-oxygen-level-dependent (BOLD) response in the targeted regions after 3-mA tDCS, (3) changes in functional connectivity of executive control networks after 3-mA tDCS, and (4) associations between changes in performance and functional connectivity in patients with SCZ. We hypothesized that compared to sham, 3-mA prefrontal tDCS will improve working memory performance, increase frontal activation, and strengthen executive network connectivity. We also expect that those with greater improvements in connectivity will exhibit better performance. Investigating the neurophysiological effects of intensified tDCS can inform the optimization of tDCS protocols for SCZ.

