#### 2.10.3 Exploratory outcomes

We will perform exploratory analyses to investigate the correlations between changes in physiology and changes in cognitive performance before and after tDCS. This approach allows us to assess the intricate relationship between brain function and behavior. Furthermore, our objective is to identify potential predictors of variations in working memory task performance and individual responses to the intervention, taking into account a range of clinical and biological measures. In addition, we will incorporate the induced electric field (E-field) in the prefrontal area for each participant. This E-field is determined through an analysis of the computational finite-element model with simNIBS software and is considered as a potential predictor of how the brain responds to tDCS.

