### 2.12 Statistical methods

To assess the efficacy of the tDCS intervention, we will conduct a mixed model analysis of variance (mixed-ANOVA) on the n-back task indices, including d-prime, reaction time, and accuracy with time (before and after tDCS) as the within-subject factor and group (active tDCS and sham tDCS) as the between-group factor and their interaction. The group × time interaction effect and the main effect of group and time will be explored to see if changes in working memory performance and brain activation (two key dependent variables) are influenced by the type of stimulation (group factor) and time (before vs during stimulation). The normality and homogeneity of data distribution, and variance will be confirmed by Shapiro-Wilk and Levin tests, respectively. Mauchly’s test will also be used to evaluate the sphericity of the data before performing the ANOVA. In case the assumption of sphericity was violated, the degrees of freedom were corrected using Greenhouse-Geisser estimates of sphericity. To investigate the associations between changes in brain activity/connectivity and task performance changes, we will employ the Pearson correlation test. This test will help identify potential relationships between changes in brain activity and task performance, providing valuable insights into the neural mechanisms underlying our observations. All statistical analyses will be conducted using R [45].

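### The exploratory brain-behaviour correlation is given no term for arm; if read as pooled over arms, a tDCS effect on both measures alone makes it positive

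*Protocol article*

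**What the plan says.** The fourth objective in the Introduction is to examine "associations between changes in performance and functional connectivity in patients with SCZ". The hypotheses that follow have two parts. The first is about the arms: "compared to sham, 3-mA prefrontal tDCS will improve working memory performance, increase frontal activation, and strengthen executive network connectivity". The second is about individuals: "We also expect that those with greater improvements in connectivity will exhibit better performance".

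Section 2.10.3 gives the analysis its status, under exploratory outcomes: "exploratory analyses to investigate the correlations between changes in physiology and changes in cognitive performance before and after tDCS".

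Section 2.12 gives the method: "To investigate the associations between changes in brain activity/connectivity and task performance changes, we will employ the Pearson correlation test". It adds that the result should inform the mechanisms behind the observations. The same section brings arm into the mixed ANOVA, with "group (active tDCS and sham tDCS) as the between-group factor and their interaction", but does not mention arm for the correlation. Nowhere does the article describe a within-arm, partial or arm-adjusted correlation.

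**The concern.** A bivariate Pearson correlation has no place for arm. If it is computed over all participants, it mixes two sources of association. One is the tendency, among patients who had the same stimulation, for larger connectivity gains to go with larger performance gains. The other is the distance between the two arm means on both measures. The individual-level hypothesis concerns only the first.

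The second source appears whenever tDCS shifts both measures, which is what the trial hopes to show. Success on the arm-level hypotheses would then push the pooled correlation towards the answer expected for the individual-level one. At stake is the mechanistic reading: a significant pooled correlation could not separate performance change tracking connectivity change from the same stimulation having moved both.

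**Working it through.** **Inputs from the article**
- Allocation: "either a single session of active (n = 24) or sham (n = 24) tDCS" (Abstract, Methods). The minimum sample before the dropout allowance is 42, or 21 per arm (section 2.5).
- Planning effect for working memory: f = 0.25, two groups, three measurements, alpha 0.05, power 95% (section 2.5).

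**Inputs assumed**
- The correlation is pooled over arms.
- The arm differences in the two change scores, in within-arm SD units, are dx (connectivity) and dy (performance). The article gives no effect size for connectivity.
- The correlation between repeated measurements, rho, is not stated. I use 0.5 and show 0.3 and 0.7.
- The within-arm correlation of the two changes is zero. This is the null for the individual-level hypothesis.

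**Step 1. The plan's own figure.** No figure is given for the correlation, so I check the sample size that carries the planning effect. For the group by time interaction, lambda = f² × N × m / (1 − rho) = 0.0625 × 42 × 3 / 0.5 = 15.75, with 2 and 80 degrees of freedom and sphericity assumed. Power is 94.6% at N = 42 and 95.6% at N = 44. The stated 42 is reproduced closely.

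**Step 2. What f = 0.25 means for a change in performance.** With two time points, d = 4f / √(2(1 − rho)):
- rho = 0.3: 1 / √1.4 = 0.85
- rho = 0.5: 1 / √1.0 = 1.00
- rho = 0.7: 1 / √0.6 = 1.29

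With the three planned measurements and rho = 0.5, the SD of a change equals the SD σ of a single measurement, and the baseline-to-online difference depends on the time profile, where δ is the largest arm difference:
- Effect during stimulation only, or fully kept at 24 h: δ²/18 = 0.0625σ², so d = 1.06.
- Linear build-up to 24 h: δ²/24 = 0.0625σ², so δ = 1.22σ at 24 h and d = 0.61 online.
- Half faded by 24 h: the same equation, with d = 1.22 online.

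A performance effect near 1.0 SD is therefore plausible but not fixed by the plan.

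**Step 3. The pooled correlation with no within-arm association.** For 1:1 arms,

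r = (dx·dy/4) / √((1 + dx²/4)(1 + dy²/4)).

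Example with 1.0 SD on both: 0.25 / 1.25 = 0.20.

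**Step 4. Rejection rates.** Two-sided 5% tests, simulated with 24 per arm:

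| Arm effects on the two changes | Pooled r | Pooled Pearson rejects | Arm-adjusted rejects |
|---|---|---|---|
| 1.0 and 0 SD | 0 | 5% | 5% |
| 0.5 and 0.5 SD | 0.06 | about 7% | 5% |
| 1.0 and 0.5 SD | 0.11 | about 11% | 5% |
| 0.8 and 0.8 SD | 0.14 | about 16% | 5% |
| 1.0 and 1.0 SD | 0.20 | about 28% | 5% |

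At 21 per arm, 1.0 SD on both gives about 25%. The product of the two effects drives the bias, so a small effect on either measure keeps it small: 1.0 SD on one and 0.3 SD on the other gives about 7%.

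**The case against.** **The article does not say that the arms are pooled.** This stands. Correlations computed separately in each arm are also Pearson correlations and would remove the problem, and the reference to patients with schizophrenia describes everyone in the trial. A reader might infer that the plan commits to pooling; it does not. Pooling is only the natural reading of an objective set for all patients and a method in which arm is not mentioned. The point survives because the single method named has no place for arm, while the section does name arm for the ANOVA.

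**The analysis is exploratory.** This also stands and limits the weight of the point. Exploratory status excuses low power and a loose error rate. It is a weaker excuse for a predictable bias towards the expected answer, since the analysis is also a numbered objective with a directional expectation.

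**The large figures need large effects on both measures.** Correct. A reader might take 28% as the error rate implied by the trial's planning effect. The article does not support that: f = 0.25 is planned for working memory over three measurements, rho is not given, and there is no planning effect for connectivity.

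**A pooled correlation is a valid estimate of the overall association.** True, if that association is all that is claimed. It does not answer the individual-level expectation or support a mechanistic reading, and the article wants both.

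**Conclusion.** The point holds in a limited form and is minor. Read as pooled, the named test cannot support the individual-level expectation or a mechanistic reading if tDCS shifts both measures. The rejection rate under no within-arm association then runs from about 7% (0.5 SD on both) to about 28% (1.0 SD on both) at 24 per arm, against 5% with adjustment for arm. These figures rest on pooling and on arm effects that are assumed, wholly so for connectivity.

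Two stronger readings are tempting and do not hold. One is that the correlation misleads whenever the treatment works: if tDCS improves performance without moving connectivity, the rate stays at 5%. The other is that the trial's efficacy result is in doubt: that result comes from the mixed ANOVA, which includes arm and its interaction with time, and none of the primary outcomes uses this correlation.

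**What to change.** In section 2.12, replace the plain Pearson test with a regression of performance change on connectivity (or activity) change with arm as a covariate; a partial correlation given arm is equivalent. Report the correlation within each arm descriptively, and base any statement about mechanism on the arm-adjusted coefficient. If separate within-arm correlations were always intended, say so in the same sentence.

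The cost is one sentence and one degree of freedom, with no new data. A connectivity-change by arm interaction is optional; it uses one more degree of freedom and would have low power at this size. The article describes recruitment as under way, so the change can be made before analysis.

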## 3. Discussion

The present study is a double-blind, sham-controlled, parallel-group trial designed to investigate the effects of the 3-mA tDCS over the left and right DLPFC on working memory and brain physiological correlates (cortical activation, connectivity) in patients with SCZ using tDCS and fMRI. Given that cognitive deficits play a causal role in daily functioning of patients with SCZ [51] and the potential of tDCS as a cognitive boosting treatment, it is crucial to understand the mechanisms of effects of tDCS in SCZ in order to optimize the intervention. While cognitive effects of tDCS are already investigated in SCZ [8, 19], no study investigated the impact of 3 mA intensity as well as a tDCS-fMRI paradigm in SCZ.

The results of this study are helpful in optimizing tDCS protocols in SCZ and inform us of neurocognitive mechanisms underlying the interventions in several key ways. Elucidating the neurophysiological mechanisms of intensified 3-mA prefrontal tDCS will clarify how modulating frontal regions impacts local and network-wide activity to enhance cognition [23]. Understanding these neural substrates reveals how tDCS strengthens critical circuitry impaired in SCZ, as shown by frontal lobe abnormalities in this disorder [6, 7]. Identifying predictive biomarkers of tDCS response using fMRI will enable personalized targeting of tDCS to each patient’s brain activity profile. Connectivity patterns may predict behavioral and physiological responses, as dosage-dependent effects on cognition have been observed [19]. Machine learning can develop prognostic models to optimize individualized protocols. Gaining fundamental knowledge of intensified tDCS effects on SCZ pathophysiology will facilitate developing cortically-targeted cognitive treatments. Clarifying relationships between prefrontal modulation and cognitive gains provides a framework for interventions, given that frontal cognitive deficits underlie much of the disability in SCZ [3].

This study will additionally deliver initial safety and efficacy data on an intensified tDCS protocol to support larger clinical trials. Positive results could lead to rapid broader testing of a promising tool for debilitating symptoms that affect the majority of SCZ patients [1]. In summary, this research converges methodologies to optimize non-invasive brain stimulation for cognition in SCZ–a disorder where such interventions are greatly needed.

## List of abbreviations

SCZ: schizophrenia
tDCS: transcranial direct current stimulation
DLPFC: dorsolateral prefrontal cortex
fMRI: functional magnetic resonance imaging
BOLD: blood-oxygen-level-dependent
